### Sample size

Sample size calculations were based on estimated effect sizes for the primary outcome. A recent meta-analysis [3], indicated that lesson planning and delivery interventions have a pooled effect of *d* = 0.60 on MVPA during PE lessons. To ensure 80 % power to detect an effect of this size would require 90 participants in a non-clustered trial (two-tailed probability level of 0.05). We considered the clustered nature of the data, including both school and class levels [46]. However, results from recent studies of MVPA in PE lessons indicated that clustering at the school level was negligible after accounting from clustering at the class level [22, 33]. As a result, we adjusted our sample size calculations for clustering using the formula 1 + (*m*-1)ρ, where *m* is the number of students per class and ρ is the intra-class correlation (ICC) [46].

Our recent study in Sydney-area schools indicated a class-level ICC of 0.62 [22], which was similar to Aelterman et al. [33] who reported a class-level ICC of 0.63. With an estimated class size of 22 participating students, an adjustment of 14.23 was required: 1 + (22–1)*0.63 = 14.23. Multiplying by the 90 participants required in non-clustered trial, we estimated that 1280 students would need to participate to achieve 80 % power. We estimate that 14 schools, with a mean of 4.5 classes of Year 8 students per school can be recruited and, therefore, aim to recruit 1386 students (14 schools × 4.5 classes per school × 22 students per class). Potential loss to follow up of up to 30 % of participants (*n* = 384; a very conservative estimate) will not substantially impact on the statistical power of the study. This resilience to loss of power exists because this study will use generalized mixed models, enabling the inclusion of all participants (included at baseline) in the analyses. In non-clustered longitudinal clinical trials, this analytic approach has been shown to yield similar point estimates and smaller decreases in statistical power than multiple imputations [47, 48].

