Generalized linear mixed models will be also used to examine mediation hypotheses. Mediating effects will be estimated using a cluster-bootstrapped based product-of-coefficients test that is appropriate for cluster randomized controlled trials [75].

Potential moderators of the intervention effects will also be explored. Potential moderators will include gender and ethnic background (categorical variables), as well as socio-economic status and baseline levels of physical activity and psychosocial variables (e.g., motivation and needs satisfaction) which will be treated as continuous variables. Moderator effects will be explored using the same generalized mixed modeling approach by including appropriate interaction terms in the regression models. The trial is powered to detect main effects, not interactions; thus, we will employ a less stringent significance level to explore potential moderators. Interaction terms that are significant at *p* < 0.1 will be explored by testing differences in intervention effects across sub-groups stratified according to the moderator variable [76].

Per protocol analyses will investigate the influence of teachers’ adoption of the intervention, as indicated by the proportion of intervention components completed by each teacher (e.g., workshops attended and online tasks completed), on student outcomes (e.g., MVPA during PE lessons). Analyses will also examine the effect of teachers’ implementation of the intervention, as indicated by increases in their use of AMPED teaching strategies from baseline to post-intervention (observed in video recordings of their lessons), on student outcomes.

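### Continuous moderators that pass the p < 0.1 interaction test are re-tested in cut sub-groups, which gives less precise, cut-dependent effects than the model already fitted

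*Protocol article*

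**What the plan says.** The moderator plan is one paragraph of the protocol article, under Statistical analysis. Gender and ethnic background are categorical moderators. The others are socio-economic status and "baseline levels of physical activity and psychosocial variables (e.g., motivation and needs satisfaction) which will be treated as continuous variables".

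The first step is a model-based test: "Moderator effects will be explored using the same generalized mixed modeling approach by including appropriate interaction terms in the regression models". The level is relaxed to p < 0.1 because "The trial is powered to detect main effects, not interactions".

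The second step applies to every interaction term below that level. Such terms "will be explored by testing differences in intervention effects across sub-groups stratified according to the moderator variable". The sentence does not separate categorical from continuous moderators. It gives no cut-point, number of strata or significance level for the follow-up.

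**The concern.** For gender and ethnic background the second step is natural, because the strata already exist. For a continuous moderator, strata exist only after the variable has been cut. Read as written, the plan keeps these variables continuous for the first test and then requires them to be categorised for a second test of the same interaction in the same students.

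That second test brings no new evidence and ignores how the effect varies within each stratum. Two things follow:

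- The sub-group effects, which readers are likely to carry away, are less precise than the fitted model can give, and they shift with the position of the cut.
- The sub-group test can disagree with the interaction that triggered it. A reader could then be shown a significant continuous interaction beside a non-significant sub-group difference, with nothing but the coarser scale to explain the gap.

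**Working it through.** **Figures in the plan.** No power or precision is stated for any moderator analysis, so there is no moderation figure to reproduce. The main-effect sample size does reproduce: 1 + 21 × 0.63 = 14.23, and 90 × 14.23 = 1280.7 against the stated 1280. It has no bearing on this point.

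**Inputs.** From the Statistical analysis section: continuous moderators, and an interaction test at 0.10. Assumed, because the article does not give them:

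- a normally distributed moderator and linear moderation;
- two-sided tests, with 0.10 also used in the follow-up;
- a median split or outer tertiles as the cut;
- first-step power of 50% to 90%.

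**Step 1: information kept after cutting.** This is the efficiency of the cut comparison relative to the continuous linear interaction.

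- Median split: 2/π = 0.637.
- Outer tertiles (upper against lower third, middle third dropped): the 2/3 quantile of the standard normal is 0.431, with density 0.3636 there. The mean of the upper third is 3 × 0.3636 = 1.091. Efficiency = (2/3) × 1.091² = 0.793.

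The relative standard error is 1/√efficiency: 1/√0.637 = 1.25 for the median split and 1/√0.793 = 1.12 for outer tertiles.

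**Step 2: how often a moderator that has passed then misses in the sub-group test.** Let δ = 1.645 + z(power) be the expected value of the continuous test statistic. The cut statistic has expected value δ√efficiency. Its correlation with the continuous statistic is √efficiency, which is 0.798 for the median split and 0.891 for outer tertiles. The two statistics are taken as bivariate normal. The quantity wanted is 1 − P(both significant) / P(first significant).

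Worked case, 80% first-step power and median split: δ = 1.645 + 0.842 = 2.486, and the cut statistic has mean 2.486 × 0.798 = 1.984. P(both significant) = 0.606, so the miss rate is 1 − 0.606/0.800 = 24%.

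| First-step power | Misses after a pass, median split | Misses after a pass, outer tertiles |
|---|---|---|
| 50% | 36% | 23% |
| 80% | 24% | 14% |
| 90% | 18% | 9% |

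**Step 3: does the second test at least filter out false leads?** With no true interaction (δ = 0), a term that passed at 0.10 is significant again after a median split about half the time (0.049/0.10 ≈ 49%). The second test therefore drops some real moderators and is a weak check on false ones.

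**Sensitivity.** The miss rates move with the assumptions. At 30% first-step power the median-split miss rate is 42% (58% significant after a pass). If the follow-up used a two-sided 0.05 level, a median split would miss 38% of the time at 80% first-step power (62% significant after a pass). The efficiencies in Step 1 do not depend on power or significance level, only on the normal moderator, the linear form and the cut.

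**The case against.** The strongest reply is that the continuous interaction term decides whether there is moderation, and that test uses full information. This is correct. A reader might infer that the plan loses power to detect moderation. Under the same assumptions a median split in place of the continuous test would lower 80% power to 63%, and outer tertiles would lower it to 72%. The documents do not support that inference, because the cut test does not replace the interaction test. It runs only after the interaction test is passed, so those unconditional figures do not describe it. For the same reason the relaxed 0.1 level is not undone: it governs the first step, which stays continuous.

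A reader might also infer that a non-significant sub-group contrast overturns the interaction. The article contains no such rule. It speaks of exploring, and nothing in it prevents the continuous coefficient from being reported.

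It can also be said that cut-points belong in an analysis plan that is not shown. Their absence is indeed no fault of an article. But any cut-point supplied later would still discard information, so the point concerns the method stated and not a missing detail.

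Finally, little depends on this. Moderation appears in none of the research questions or hypotheses, the article says the trial is not powered for interactions, and strata do not assume linearity. All of that stands. It limits the weight of the point without making the cut test the better follow-up.

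**Conclusion.** The point holds as a minor one. The first step is sound. The follow-up, as worded, sends continuous moderators to a sub-group test that keeps about 64% (median split) or 79% (outer tertiles) of the information, given a normal moderator and linear moderation. The resulting effects depend on the cut and can disagree with the interaction that led to them.

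The miss rates of 18% to 36% and 9% to 23% are illustrations. They rest on an assumed two-sided 0.10 level at both steps and first-step power of 50% to 90%, none of which the article gives for the follow-up. No primary, secondary or mediation result is affected.

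**What to change.** Limit the sub-group follow-up to gender and ethnic background. For continuous moderators, wording such as this would do:

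*For continuous moderators, the continuous interaction with its confidence interval is the moderation result. Where it reaches p < 0.1, the model-based intervention effect will be reported with 95% confidence intervals at the 10th, 25th, 50th, 75th and 90th percentiles of the moderator. Linearity will be checked with a quadratic or spline interaction term. Strata may be shown for description but will not be tested.*

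The cost is a few lines of wording and post-estimation contrasts from a model already being fitted, with no new data. The small downside is reliance on a linear or spline form, which the linearity check addresses.

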## Discussion

The purpose of this study is to evaluate an intervention designed to increase the amount health-enhancing PA that secondary school students accumulate during their school-based PE lessons. The intervention brings together, for the first time, strategies designed to maximize opportunities for students to be active with strategies intended to enhance their motivation for PA. The intervention is delivered, in part, using an online training platform for teachers that will help facilitate more widespread dissemination compared with interventions that rely exclusively on face-to-face training.

## Abbreviations

AMPED: Activity and Motivation in Physical Education
BMI: body mass index
ICC: intra-class correlation
MVPA: moderate-to-vigorous physical activity
NSW: New South Wales
PA: physical activity
PE: physical education
RCT: randomized controlled trial
SDT: self-determination theory
SES: socioeconomic status
